## Rigour

### Treatment fidelity

Threats to treatment fidelity will be minimised by providing the SEPRP, PNPP and PPP programmes within the context of comprehensive, structured curriculum documents and through delivery of training by members of the research team. Each programme will be audited in week 4 or 5 to assess adherence to programme principles. An action plan will be implemented if there are any concerns regarding adherence to programme content and principles. Providing PNPP participants with structured feedback (Component 4 above) will also enhance treatment fidelity.

### Data Integrity

Data integrity will be enhanced by having data collection performed by a small number of trained research assistants and by adherence to assessment protocols.

Errors will be logged and remedial strategies implemented as required. The central study processes (e.g. eligibility assessment, outcome assessment etc.) will be kept under review to add to the rigour of the study.

Single data entry into SPSS will be performed with visual verification of a sample of records from the data set created from the single entry using a continuous sampling plan (CSP-1) (after [39]). A CSP-1 gives the number of successive records with no data entry errors that must be inspected *i *before a random sample fraction *f *of records will begin. Whenever an error is found, the error is corrected and the successive record checking using i is repeated.

### Adverse events

All adverse events that occur after informed consent will be recorded on an Adverse Event Recording Form (AERF) and reported to the patients General Practitioner within the respective practice and to the principal investigators. The PRINCE team have provisionally defined an adverse event as 'Any acute alteration in the patient's physiological condition'. A protocol for dealing with adverse episodes has been developed and is included as part of the training programme for the research assistance and practice nurses.

All research assistants will be trained in basic life support and will carry emergency resuscitation equipment to all patient assessments. Physiotherapists will also bring resuscitation equipment to each programme session.

## Pilot study

A pilot study will be conducted with one GP practice. This pilot will be used to identify problems with the research design/processes; refine data collection and analysis; assess adequacy of data sources; examine selection and enrolment processes; and assess the participants' perspective on participating. We will not include data from the pilot period in the main analyses of the trial.

## Embedded Qualitative Study

## Introduction and design

To enhance the overall design of the study a qualitative strand was added. This approach is described as an "embedded design" [40]. Embedded designs are used when the inclusion of qualitative data would be helpful in addressing secondary research questions within the larger quantitative study [40]. The overall aim of the embedded qualitative study is twofold: (1) to examine the *proces*s of the intervention and (2) to define *usual care*. The specific aims of this element of the study are to:

• understand participants perceptions of COPD and its impact on their day-to-day lives;

• determine the components of usual care for participants allocated to the control group;

• understand individuals approach to and experiences of managing COPD prior to the SEPRP;

• understand the impact that the SEPRP may have on participants' self-management skills;

• gain insights into the factors that govern adherence to programme principles.

## Grounded Theory

A grounded theory methodology (after Corbin and Strauss [41]), was chosen to guide the qualitative element of this study because of its focus on how people respond to and act towards the problems they encounter [41,42]. Grounded theory aims to produce a theory to "fit" (i.e. has relevance) the situation, aid understanding and guide action and practice [41]. These are important considerations when studying health related problems. Grounded theory 'discovers' theory through systematic data collection and analysis [41].

## Data collection Methods

In-depth, one-to-one interviews (guided by an interview guide) will be the primary method of data collection. Participants will be interviewed on three occasions (1) prior to the participating in the SEPRP programme (2) within 2-6 weeks of completing the SEPRP and (3) three months after completion of the programme. This longitudinal design will enable understanding of the reasons for participant's changes (or not maintaining change) in self-management skills and their exercise regimes over time.

In addition, observational data (guided by an observation schedule) will be collected from one session of the SEPRP for each group from which the sample is drawn. This data will help set the interviews in context. In addition to providing contextual data, the literature suggests that the group experience (the synergistic effect of the group) may be an important factor in behaviour maintenance. Observational sessions will be of two hours duration i.e. observing a one-hour SEPRP delivered by the practice nurse (detailed in Table 2) and one-hour delivered by the physiotherapist where participants complete an exercise circuit.

## Sampling in the intervention group

Twenty participants will be recruited from those allocated to the intervention group using purposive sampling initially and theoretical sampling later on (guided by data analysis) to ensure diversity of experiences. Theoretical sampling is the process of simultaneously collecting, coding and analysing data to generate theory [41]. Grounded theorists do not seek representativeness of people or events but the representativeness of "concepts" [41]. Sampling decisions are driven by "... *concepts that emerged from analysis and that appear to have relevance to the evolving theory" *[43]. To ensure participant diversity in the initial purposive sample, the following inclusion criteria will be used:

• *Severity of COPD *- people with moderate to severe COPD (as defined by the study protocol) will be included;

• *GP practice size *- people attending GP Practices with (1) between 2,500 and 5,000 patients and (2) over 5,000 patients will be included;

• *Gender *- both men and women will be included;

• *Location of practice *- urban and rural practice settings will be included.

Purposive sampling will be superseded by theoretical sampling as the study progresses. Theoretical sampling may indicate the need to include more diverse participants and will evolve as the study progresses.

## Sampling in the control group

Structured qualitative interviews will be conducted with ten patient participants and ten practice staff (either practice nurses or GPs) from the control group. These participants will be interviewed on one occasion only. This data will be used to define and describe usual care.

## Sampling of staff delivering the SERPS

All practice nurses and physiotherapists who delivered the SEPRP will be interviewed. This interview will focus on their experience of delivering the SEPRP. This data will provide contextual information and insight into *how *staff delivered and their *experience *of delivering the SERPS.

## Analysis

The constant comparative technique [41] will be used to analyse data. Data from each group will be analysed individually (within group) and, in the case of participants who completed the SEPRPS i.e. completed three interviews (across group), to explore the impact of time on the impact of the SEPRPS. Data will be analysed in stages (e.g. all the interviews from a practice) reflective of recruitment phases. This approach enables data analysis to guide data collection and sampling decisions (theoretical sampling).

## Economic Evaluation

The economic evaluation explores the cost effectiveness of the PRINCE intervention relative to usual care for patients with COPD in Ireland. This involves the identification, measurement and valuation of all relevant costs and benefits. The time horizon is equivalent to that of the follow up for the cluster randomised controlled trial. Retrospective data on resource use is collected at baseline and 22 weeks later at the end of the study. Although the time period is relatively short, the hypothesis is that there will be positive changes in resource use for the intervention group, most likely a reduction in the probability of being hospitalised, which will yield significant levels of savings [44]. Incremental cost effectiveness analysis is used, whereby we estimate the differences in mean cost and mean effectiveness across treatment arms, and relate the difference in mean cost to the difference in mean effectiveness. Uncertainty surrounding the incremental results is assessed using cost effectiveness acceptability curves, which will present the weight of evidence in favour of intervention relative to control.

With respect to costs, we consider both the healthcare resource requirements and the private patient expenses associated with each treatment group.

Specifically, we collect data on three areas of resource use alongside the trial: Intervention costs, which include all the resources required to organise and implement the Structured Pulmonary Rehabilitation Programme in clinical practice, Other healthcare services costs, which includes the use of all primary and secondary care over the course of the trial, including both community-based care and hospital care, patient out-of-pocket expenses, which includes the individual's own time input in the treatment process and associated travel expenses.

In terms of effectiveness, our outcome measure of choice is the Quality Adjusted Life Years (QALYs). The QALY is a composite measure of health gain which simultaneously incorporates the impact of treatment in terms of health related quality of life and life expectancy. Health related quality of life data, as measured by the Euroqol (EQ5D) questionnaire, is collected alongside the clinical trial and baseline and follow up values will be combined to estimate QALY gains for each individual, and for each treatment arm.

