### Secondary

1. Incremental Shuttle Walking Test;

2. Self-Efficacy for Managing Chronic Disease 6-Item Scale [26];

3. Economic analysis specific:

a) EuroQol EQ-5D [27];

b) Utilisation of health care Service Utilisation of health care Service. For variables, i to v, we are dependent on practice notes for their determination. Based on our previous experience [28,29] we consider these to be reliable and valid:

i) Hospital admissions/length of stay;

ii) Attendance at the emergency department;

iii) Outpatient attendances;

iv) Attendance at/by GP;

v) Attendance at/by Practice Nurse;

vi) Attendance at/by Public Health Nurse;

vii) Attendance at/by Physiotherapy;

viii) Attendance at/by Social Worker;

ix) Attendance at/by Dietician;

x) Outpatient attendances;

xi) Attendance at/by consultant;

xii) Utilisation of Home help;

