## Randomisation

### Random allocation sequence generation

Randomisation is at the level of the general practice (cluster). The random allocation sequence will be generated using a computer generated random number list [35]. To minimise the time delay between practices agreeing to participate and the commencement of the training programme for practice nurses and the implementation of the intervention for experimental clusters and patients therein, practices will be randomised in blocks of clusters when all patient participants in the block of clusters have been recruited. We propose to randomise clusters in four groups of clusters on a 1:1 ratio. This approach is recognised as a legitimate means of overcoming long delays between recruitment and implementation of the intervention in cluster trials [36].

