## Quantitative Analysis

The analysis will be based on the GP Practice with the patient as the unit of analysis whilst accounting for the intracluster correlation coefficient. Analyses will be by intention to treat. Quantitative data will be analysed, in aggregate, using The Statistical Package for the Social Sciences (SPSS, v17) and R ([37], 2.11). Data will be entered into SPSS, coded, cleaned and locked before any analyses are made. Only members of the research team who needed access to the database to fulfil their roles within the study were granted access to the database. Funders did not have access to the database at any time. Demographic characteristics of the practices and the participants within the practices will be described using percentages, measure of central tendency (means or medians) and measures of variation (standard deviations or ranges). Comparability of randomised groups by socioeconomic and other categorical baseline variables will be by the chi-square (*X*^2^) test.

Whilst every effort will be made to exclude all confounders at the design phase of the study, this is not always possible. The analysis of data will therefore include the search for and control of nuisance variables for which adjustments had not been made. In particular, a mixed effects model will be used to model the longitudinal change in the mean scores for each of the four dimensions of the CRQ primary response while adjusting for explanatory variables and baseline CRQ as needed and incorporating random effects to model the homogeneity within cluster and the correlation within patient across time. The Akaike information criterion (AIC), for linear mixed-effects models in the analysis of clustered data, will be used to decide between candidate models [38]. The significance level will be set at α = 0.05 for all analyses.

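### Incremental QALYs and costs are compared as arm means, with baseline EQ-5D built into the outcome and no stated role for baseline EQ-5D or baseline cost as a covariate; adding both, and carrying practice clustering through to the acceptability curve, is a free improvement

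*Protocol article*

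**What the plan says.** The Economic Evaluation section of the protocol article describes its own procedure. For EQ-5D, "baseline and follow up values will be combined to estimate QALY gains for each individual, and for each treatment arm". The incremental analysis follows: "we estimate the differences in mean cost and mean effectiveness across treatment arms", with the cost difference then related to the effectiveness difference. On uncertainty, "Uncertainty surrounding the incremental results is assessed using cost effectiveness acceptability curves". On costs, "Retrospective data on resource use is collected at baseline and 22 weeks later at the end of the study". The section names no covariate, no model and no way of generating the curve.

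The Quantitative Analysis section opens with a general statement that the analysis is done "with the patient as the unit of analysis whilst accounting for the intracluster correlation coefficient". It then sets out a mixed model for the four CRQ dimensions, "adjusting for explanatory variables and baseline CRQ as needed and incorporating random effects to model the homogeneity within cluster". That model is spelled out for the CRQ only. EQ-5D and service use appear among the secondary outcomes, under the label "Economic analysis specific". Allocation is by general practice.

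**The concern.** A QALY computed from two EQ-5D readings contains the pre-randomisation value. If that value is only an ingredient of the outcome, the comparison of arm means depends on how well the arms happened to match at baseline.

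- If the QALY is the area under the line joining the two readings, a baseline imbalance passes straight into the difference.
- If the gain is measured from each patient's own baseline, the imbalance is subtracted in full. That is too much, because follow-up scores regress toward the mean.

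Using baseline EQ-5D as a covariate avoids both problems. The same reasoning applies, less sharply, to costs: prior resource use predicts later resource use, and it is being collected anyway.

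Over 22 weeks any true QALY difference is small, so a modest baseline difference can be as large as the effect sought. Cost effectiveness is one of the four main objectives of the trial, so this precision is worth having. A separate, conditional matter is whether the clustering allowance made for the other analyses reaches the cost and QALY differences and the curve.

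**Working it through.** **1. The plan's own figure.** The Sample Size Estimation section gives a difference of 0.5, SD 1.145, ICC 0.05, 80% power, alpha 0.05 (taken as two-sided), at least 10 patients per practice, 20% loss of participants and 4 practices lost.
- Per arm without clustering: 2 × (1.145 × (1.960 + 0.842)/0.5)² = 82.3.
- Patients analysed per practice: 10 × 0.8 = 8. Design effect: 1 + (8 − 1) × 0.05 = 1.35.
- 82.3 × 1.35 = 111.1 per arm, or 27.8 practices in total, rounded to 28. Adding 4 gives 32, as stated.

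The steps below use 28 practices of 8, that is 112 patients per arm. The article gives no sample-size figure for the economic analysis.

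**2. Inputs not in the article (assumptions).** Baseline to follow-up EQ-5D correlation r = 0.4 to 0.7; equal EQ-5D SD at both times, 0.25 (range 0.20 to 0.30); ICC 0.05 for EQ-5D and cost, borrowed from the CRQ calculation (range 0 to 0.10). The horizon T = 22/52 = 0.423 years is from the article.

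**3. Variance per patient,** with B and F the baseline and follow-up EQ-5D and s their SD.
- Area under the curve, T(B + F)/2: variance T²s²(1 + r)/2.
- Change-based gain, T(F − B)/2: variance T²s²(1 − r)/2.
- Either one with B as a covariate: variance T²s²(1 − r²)/4.

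Ratios to the adjusted analysis:

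| | Formula | r = 0.4 | r = 0.7 |
|---|---|---|---|
| Area under the curve | 2/(1 − r) | 3.3 | 6.7 |
| Change | 2/(1 + r) | 1.4 | 1.2 |

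**4. Shift in a realised sample.** Given a baseline imbalance d, the expected shift in the QALY difference is (T/2)(1 + r)d for area under the curve and (T/2)(r − 1)d for change. With T/2 = 0.2115 and d = 0.05:
- Area under the curve: 0.2115 × 1.4 × 0.05 = 0.0148 (r = 0.4) to 0.2115 × 1.7 × 0.05 = 0.0180 (r = 0.7).
- Change: 0.2115 × (−0.6) × 0.05 = −0.0063 to 0.2115 × (−0.3) × 0.05 = −0.0032.
- For scale, a true difference of 0.05 at follow-up, with balanced baselines, contributes 0.2115 × 0.05 = 0.0106.

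**5. How likely such an imbalance is.** The SE of the baseline difference is 0.25 × √(2 × 1.35/112) = 0.0388, so the chance of an absolute difference above 0.05 is about 0.20. With SD 0.20 or 0.30 the SE is 0.0311 or 0.0466, and the chance about 0.11 or 0.28.

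**6. Clustering, only if practice were ignored.** The correct SE is √(1 + (m − 1) × ICC) times the unclustered one.
- ICC 0.05, m = 8: √1.35 = 1.162, so the unclustered SE is 1 − 1/1.162 = 14% too small. A nominal 95% interval covers 90.8%, and a probability of being cost-effective that should read 0.80 would read 0.84.
- Range: 1.03 (ICC 0.01, m = 8) to 1.38 (ICC 0.10, m = 10). At ICC 0 there is no effect.

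**The case against.** The strongest reply is that the article does not commit to an unadjusted analysis. A difference in mean cost and mean QALYs is what any incremental analysis estimates, and a regression with covariates and practice effects also yields one. Covariates and the resampling scheme normally sit in an analysis plan that is not shown. This reply holds against several inferences that a reader might draw:

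- *That the plan has chosen a raw comparison.* The text does not say so.
- *That it leaves out baseline EQ-5D.* It does not: baseline EQ-5D enters the QALY. Only its use as a covariate is unstated.
- *That it ignores clustering.* The general sentence in the Quantitative Analysis section is not limited to the CRQ, and EQ-5D and service use are listed trial outcomes, so it may well cover them.
- *That baseline imbalance makes the acceptability curve overconfident.* It does not. Under randomisation, chance imbalance is part of the sampling variation that a valid unadjusted standard error already reflects. Only ignored clustering would make the curve too sure.

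It is also fair that the article's word is gains. If these are change-based, the smaller figures apply.

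What remains does not rest on silence alone. The section gives baseline EQ-5D a specific job, as a component of the outcome, and then compares arm means. Carried out as written, that is less efficient than it need be under either reading of gain.

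**Conclusion.** The point holds as a recommended improvement to the comparison that the Economic Evaluation section states; it is not an error that invalidates the analysis. Without baseline EQ-5D as a covariate, the variance of the incremental QALY is inflated 3.3 to 6.7 times if QALYs are areas under the curve, or 1.2 to 1.4 times if they are change-based. A 0.05 baseline imbalance would move the estimate by 0.015 to 0.018, or by −0.006 to −0.003, respectively. These figures are at the individual level and rest on an assumed correlation of 0.4 to 0.7 with equal SDs; the article supplies neither. No size is put on the gain from baseline cost, since the article gives nothing from which to derive it.

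The clustering part is conditional. The 14% shortfall in standard errors arises only if practice is left out of the economic model, and only to the extent that costs and QALYs cluster at all. The article does not establish that practice will be left out.

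**What to change.** State in the economic analysis how QALYs are formed from the two EQ-5D readings. Estimate the incremental QALY with baseline EQ-5D as a covariate and the incremental cost with baseline cost as a covariate. Once baseline EQ-5D is in the model, area-under-the-curve and change-based QALYs give the same arm difference, so the choice between them no longer affects the result.

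In the same model, carry over the practice clustering allowance from the Quantitative Analysis section, through practice random effects or a bootstrap that resamples whole practices, keeping each patient's cost and QALY together. Build the acceptability curve from that model. Fix this before the allocation code is broken.

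The cost is a little more analysis work. EQ-5D and resource use are already collected at baseline and practice is known for every patient, so no new data or patients are needed.

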## Ethical Considerations

Ethical approval has been granted by the Research Ethics Committee of the National University of Ireland, Galway and the Irish College of General Practitioners (ICGP).

## Discussion

The results of this trial will be directly applicable to primary care settings in Ireland. Should a structured education pulmonary rehabilitation programme delivered at the level of the GP practice be found to be effective in improving patients' sense of dyspnoea and HRQoL then the findings would be applicable to many thousands of individuals in Ireland and beyond.
